## Abstract

**Background:**

Assessing HIV outcomes in key population prevention programs is a crucial component of the program cycle, as it facilitates improved planning and monitoring of anticipated results. The Joint United Nations Programme on HIV and AIDS recommends using simple, rapid methods to routinely measure granular and differentiated program outcomes for key populations. Following a program science approach, Partners for Health and Development in Africa, in partnership with the Nairobi County Government and the University of Manitoba, aims to conduct an outcome assessment using a novel, expanded polling booth survey (ePBS) method with female sex workers and men who have sex with men in Nairobi County, Kenya.

**Objective:**

This study aims to (1) estimate the incidence and prevalence of HIV; (2) assess biomedical, behavioral, and structural outcomes; and (3) understand barriers contributing to gaps in access and use of available prevention and treatment services among female sex workers and men who have sex with men in Nairobi.

**Methods:**

The novel ePBS approach employs complementary data collection methods, expanding upon the traditional polling booth survey (PBS) method by incorporating additional quantitative, qualitative, and biological data collection components and an improved sampling methodology. Quantitative methods will include (1) PBS, a group interview method in which individuals provide responses through a ballot box in an unlinked and anonymous way, and (2) a behavioral and biological survey (BBS), including a face-to-face individual interview and collection of linked biological samples. Qualitative methods will include focus group discussions. The ePBS study uses a 2-stage, population- and location-based random sampling approach involving the random selection of locations from which random participants are selected at a predetermined time on a randomly selected day. PBS data will be analyzed at the group level, and BBS data will be analyzed at an individual level. Qualitative data will be analyzed thematically.

**Results:**

Data were collected from April to May 2023. The study has enrolled 759 female sex workers (response rate: 759/769, 98.6%) and 398 men who have sex with men (response rate: 398/420, 94.7%). Data cleaning and analyses are ongoing, with a focus on assessing gaps in program coverage and inequities in program outcomes.

**Conclusions:**

The study will generate valuable HIV outcome data to inform program improvement and policy development for Nairobi County’s key population HIV prevention program. This study served as a pilot for the novel ePBS method, which combines PBS, BBS, and focus group discussions to enhance its programmatic utility. The ePBS method holds the potential to fill an acknowledged gap for a rapid, low-cost, and simple method to routinely measure HIV outcomes within programs and inform incremental program improvements through embedded learning processes.

## Introduction

### Background

Kenya has made significant strides in its HIV response, evident by the continuous decline in HIV prevalence among adults aged 15 to 49 years within the general population. HIV prevalence has dropped from a peak of approximately 10% in the mid-1990s to 4.3% in 2021 [1]. An analysis of the HIV epidemic within Kenya [2] highlights substantial heterogeneity. HIV prevalence varies geographically, ranging from 20.1% in Homa Bay County to 0.2% in Mandera and Wajir counties. Notably, HIV prevalence in Kenya is also disproportionally high among female individuals (5.5%) than among male individuals (2.9%) [3]. Furthermore, compared to the general Kenyan population, HIV prevalence is significantly higher among key populations, namely, female sex workers at 29%, men who have sex with men at 18.9%, people who inject drugs at 18%, and transgender people at 40% [4,5]. This underscores the critical importance of properly scaled and tailored interventions to address the HIV epidemic within key populations in the country [4].

In 2020, a nationwide mapping and population size estimation exercise estimated that there were 197,096 female sex workers and 61,650 men who have sex with men living in Kenya (National AIDSSTI Control Programme, unpublished data, December 2020). Approximately 20% of key populations are concentrated in Nairobi County, the largest of the 47 counties in Kenya [6]. Findings from a 2017 national study underscore the high prevalence of HIV among female sex workers and men who have sex with men in Nairobi, with self-reported rates of 22% and 27%, respectively [7]. In the same study, 91% of female sex workers in Nairobi reported using condoms with their last client, while 81% of men who have sex with men reported condom use during last anal sex [7]. Furthermore, peer educators played a significant role in outreach efforts, with 88% of female sex workers and 76% of men who have sex with men reporting contact with a peer educator within the last 3 months. The majority (82%) of both groups had undergone HIV testing within the last 3 months, while 22% of female sex workers and 27% of men who have sex with men reported that they were living with HIV. However, only 65% of female sex workers and 68% of men who have sex with men living with HIV reported being enrolled in antiretroviral therapy programs. Notably, 56% of female sex workers and 18% of men who have sex with men reported experiencing incidents of police violence within the last 6 months, respectively [7].

HIV prevention programs for key populations in Nairobi County are implemented by several partner organizations, all of whom report to the county government and the National Key Population Program, led by the Kenyan Ministry of Health, on a monthly basis (National AIDS and STI Control Programme, unpublished data, September 2023). Having up-to-date, representative, and robust data on key populations is of paramount importance for effective planning, management, and monitoring of programs and interventions aimed at addressing their needs [8]. The most recent population-based behavioral survey conducted among key populations in Nairobi dates back to 2017 [7] and did not include biological data. The absence of recent biobehavioral data among key population groups limits the ability of both county and national programs to understand the current epidemiologic situation, assess the impact of investments in HIV prevention and treatment programs for key populations, and identify gaps in program coverage. The high cost and resource requirements for implementing nationally representative, population-based integrated biobehavioral surveillance surveys factor into the relative infrequency of their deployment [8]. The availability of methods that can efficiently collect timely data among key population groups at appropriate scale and relatively low cost across diverse contexts is extremely limited [9]. Striking a balance between the need for methodological rigor and practical, adaptable approaches that are accessible to countries with diverse income levels is a pressing requirement [10].

### Objectives

Partners for Health and Development in Africa (PHDA), in collaboration with the University of Manitoba and the Nairobi County Government, aims to conduct an outcome assessment study using a novel, expanded polling booth survey (ePBS) method for data collection. This outcome assessment focuses on 2 key populations with whom PHDA works in Nairobi County, Kenya: female sex workers and men who have sex with men. The objectives of the study are to (1) estimate the incidence and prevalence of HIV; (2) assess biomedical (HIV testing, condom use, pre-exposure prophylaxis [PrEP] uptake, and HIV treatment), behavioral (knowledge and risk behavior), and structural outcomes (experiences of violence, stigma, and discrimination); and (3) gain a deeper understanding of barriers that contribute to disparities in accessing and using HIV services among female sex workers and men who have sex with men in Nairobi County, Kenya. Importantly, this study will pilot the feasibility of the novel ePBS method to measure outcomes in key population programs, with the intention of disseminating the approach for scaling up in other key population programs within and outside Kenya.

## Methods

### Study Setting

Nairobi County is the largest of Kenya’s 47 counties by population and has a robust key population program. According to the latest mapping and population size estimation exercise, Nairobi County has the highest concentration of female sex workers (n=39,227) and men who have sex with men (n=15,271) living or working in the country, or both [6]. The county has identified 2032 locations, across its 12 subcounties, where female sex workers solicit clients and 369 locations where men who have sex with men meet their sexual partners [6]. Bars (without lodging) have the highest proportion of female sex workers and men who have sex with men among these locations [6].

Importantly, same-sex sexual practices are criminalized throughout Kenya, and in 2017, Nairobi County implemented a ban on all forms of sex work [11,12]. This has contributed to the elevated levels of violence, stigma, and discrimination experienced by female sex workers and men who have sex with men [7] within the county. There are currently 4 large implementing partners responsible for prevention programs for female sex workers and men who have sex with men in Nairobi, which are funded by the Global Fund to Fight AIDS, Tuberculosis, and Malaria and the US President’s Emergency Plan for AIDS Relief. Among these partners, PHDA implements the largest prevention program in Nairobi and Kenya, serving approximately 34,000 female sex workers and 14,000 men who have sex with men. PHDA reaches these groups across all 17 counties in Kenya through an extensive network of peer educators and 9 Sex Workers Outreach Program (SWOP) clinics. To implement this program, PHDA receives funding from the US President’s Emergency Plan for AIDS Relief and technical support from the University of Manitoba and the University of Maryland, Baltimore. Furthermore, this collaboration involves Nairobi County and the National AIDS and STI Control Programme (NASCOP) [13].

### Program Science Approach

This study adopts a program science approach, which systematically applies scientific theory and empirical knowledge to answer critical programmatic questions that are generated by the program itself [14]. The approach seamlessly integrates the program cycle with research questions, strategically embedding iterative cycles of research and learning within a program, thus facilitating rapid uptake of knowledge and evidence into program operations. Furthermore, the program science approach generates embedded research agendas to address ongoing programmatic challenges [15]. In the context of this study, the research questions and study objectives have evolved from 2 primary programmatic concerns within the Nairobi County’s key population program. The first concern revolves around the absence of recent population-based data to assess program outcomes (biomedical, behavioral, and structural) pertinent to key populations in Nairobi County. The second concern is the lack of a low-cost, reliable, and easily reproducible method capable of routinely evaluating granular and differentiated program outcomes for key populations, assessing and identifying gaps in the program’s coverage, and making programmatic adjustments to address emerging challenges.

Program science emphasizes the importance of routinely identifying, quantifying, examining, and addressing gaps in program coverage, through tools, such as the effective program coverage framework, to reduce inequities in health outcomes and achieve population-level impact [16]. A program science approach underscores the importance of engaging affected communities [17] and actively works toward developing program and policy solutions to public health challenges [18]. As such, this study is conducted by PHDA in partnership with the community advisory board of the SWOP clinics and the Department of Public Health, Nairobi County.

### Research Questions

The study sets out to answer four specific research questions.

What is the HIV incidence and prevalence among female sex workers and men who have sex with men in Nairobi, Kenya?Has the program successfully met its targets related to biomedical, behavioral, and structural outcomes among female sex workers and men who have sex with men in Nairobi, Kenya?What is the estimated program coverage of the prevention services among female sex workers and men who have sex with men in Nairobi, Kenya?What are the key barriers experienced by female sex workers and men who have sex with men when accessing and using prevention services in Nairobi, Kenya?

### Outcomes for Measurement

In total, 12 outcomes will be measured to address the study’s research questions (Textbox 1). Specifically, to address research questions 1 and 2, five biomedical outcomes, 2 behavioral outcomes, and 2 structural outcomes will be measured. For research questions 3 and 4, program coverage, availability coverage, contact coverage, and utilization coverage will be measured among both key population groups, following the definitions outlined in the program science–informed effective program coverage framework [16]. HIV prevalence and incidence at the population level will also be measured.

Measured HIV outcomes among female sex workers and men who have sex with men using an expanded polling booth survey in Nairobi County, Kenya, from April to May 2023.
**Themes and outcomes**
BiomedicalPrevalence of sexually transmitted infections (STIs) symptoms, diagnosis, and treatmentConsistent condom useRoutine HIV testing (and receipt of results)Linkage to and retention in HIV treatment and careHIV viral load suppressionBehavioralSelf-reported HIV risk behaviorsKnowledge of HIVStructuralPrevalence of gender-based violencePrevalence of stigma and discriminationProgram coverageAvailability coverageContact coverageUtilization coverage

### Study Timeline

The ePBS study was designed with a quick turnaround; all activities are expected to be completed within 9 months. The data collection phase was planned to span 30 consecutive days, followed by data cleaning and analyses. Results will be finalized for dissemination at the end of the 9-month period.

### Study Team

#### Composition

A total of 4 study teams were established to manage the implementation of ePBS, and each team concurrently collected data in 4 different locations daily. Each team consisted of 6 members including a prevention officer, a key population outreach worker (a member of either key population community), a clinical officer, an HIV and testing service (HTS) counselor, and 2 qualitative researchers (1 focus group discussion [FGD] facilitator and 1 notetaker). Peer educators working in the SWOP clinics supported the study teams in participant enrollment. All ePBS team members, except the qualitative researchers, were enrolled from PHDA-SWOP clinic staff. All 4 teams were supervised by senior members (site supervisors) of the PHDA-SWOP clinic team and representatives from the Nairobi County government.

#### Study Team Training

The study team underwent a comprehensive 5-day training. The first 3 days of training included classroom instruction, during which the study’s investigators introduced and facilitated training on (1) the conceptual and theoretical underpinnings of the study (ie, the program science approach and the effective program coverage framework) [16]; (2) the ePBS methodology; (3) data collection methods and tools; (4) logistics, implementation flow, and study procedures; and (5) data entry processes. Subsequently, 2 days were dedicated to field practice during which mock data collection exercises were conducted to enhance the skills of the study team and to provide opportunities for troubleshooting any anticipated challenges in the field. Importantly, all 5 days of ePBS training prioritized practical exercises to ensure that the study team felt confident and proficient, thereby ensuring consistency and quality in data collection.

### ePBS Method

The ePBS method is a rapid, cross-sectional study design using complementary quantitative and qualitative methods for data collection. The innovative approach expands upon the traditional polling booth survey (PBS) method [19] by incorporating additional qualitative, quantitative, and biological data collection methods and an improved population-based approach to random sampling. Within the ePBS method, quantitative methods include (1) PBS, a group interview method in which individuals provide anonymous and unlinked responses to survey questions through a ballot, which has been shown to reduce reporting and social desirability biases for sensitive questions about conventionally stigmatizing behaviors, experiences, and social circumstances [19,20] and (2) behavioral and biological survey (BBS), which includes a short face-to-face, individual interview linked to the collection of biological samples (blood and urine). Qualitative methods include FGD with a subset of ePBS participants to inquire about factors that contribute to gaps in program coverage. Hence, the expansion of the traditional PBS by adding a BBS and FGD is referred to as ePBS.

Cross-sectional designs are commonly used for population-based surveys and to assess the prevalence of diseases in a population [21]. They are also useful for informing planning, monitoring, and evaluation of public health programs and interventions. In this study, we use quantitative methods to measure prevention program outputs and relevant outcomes among female sex workers and men who have sex with men participants, as outlined in research questions 1 to 3. We use qualitative methods to gain insight into the barriers affecting the accessibility and use of HIV services, as specified in research question 4.

### PBS Component

#### Overview

The PBS method is a well-established group survey method comprising only binary questions, in which individuals provide responses to survey questions by placing a token corresponding with their answer into a ballot box [22]. Individual responses remain anonymous and unlinked, ensuring confidentiality. This anonymity has been shown to enhance participants’ trust in the confidentiality of the data collection process, thereby minimizing social desirability biases and lending itself to more accurate reporting on sensitive behavioral information [23]. Data generated through PBS have been found to be comparable to the findings from other studies that used different methodologies with the same populations [20].

#### Sampling Procedure

Potential participants are selected using a 2-stage, randomized, probability-based sampling procedure and organized into small homogenous groups by key population groups (ie, female sex workers and men who have sex with men) and typology of the location at which sex work and cruising take place (eg, bar, bar with lodges, street, and clubs). Each PBS session consists of 10 to 12 participants of the same key population group who congregate and solicit clients or cruise in the same locations. Given the group interview format, the number of survey questions is intentionally limited, and each question is short and simple to facilitate easy response [22]. The key population program in Kenya has previously used PBS, and participants from different key population groups have found it to be an acceptable approach [7].

#### Implementation Procedure

The PBS component of the ePBS study was led by prevention officers and outreach workers. Conducting PBS requires materials that are not typically considered for other survey methods. First, each participant in a PBS session must have 3 different colored ballot boxes associated with yes, no, and not applicable responses (typically green, red, and white, respectively) and a set of cards to use as tokens to be dropped into the ballot boxes. Cards should be clearly numbered in alignment with the number of survey questions. Each participant’s station also requires a polling booth carton to create a private space that is not visible to other participants in the PBS session (often a cardboard box with 1 open face pointed at the participant). The facilitator at each PBS session should be equipped with copies of the standardized data collection tool (survey) and reporting forms to tally and record responses to each question.

Peer educators from SWOP mobilized 10 to 12 potential participants and invited them to participate in a PBS session, each of which was conducted as follows:

Participants invited to the PBS were provided with an individual polling booth carton at the study venue. The polling booths were separated by at least 1 m to ensure privacy and confidentiality for each participant and their responses.The facilitator welcomed the participants and explained the objective of the study, read out the consent format, provided time and space for questions, and sought informed consent from every participant.Each participant received 3 ballot boxes (green, red, and white) and a pack of cards, with each card numbered and stacked in a sequential order to correspond with the number of questions in the survey.The facilitator confirmed that each participant had the correct number of cards arranged in the proper order before proceeding with the questions.The facilitator provided a full explanation of the PBS procedure, including an example question and a practice response, to assure participants that their responses will remain anonymous and unlinked.In terms of responses, the facilitator explained the following:If the response to the question is yes, the participant should put the card with the corresponding question number into the green box.If the response to the question is no, the participant should put the card with the corresponding question number into the red box.If the question does not apply to the participant, the participant should put the card with the corresponding question number into the white box.If the person does not want to answer the question, the card with the corresponding question number should be kept outside the provided boxes.The facilitator read the survey questions, one at a time, making the exercise engaging and lively. They ensured that each question was clearly understood by all participants by (1) reading each question clearly, slowly, and loudly to ensure that each participant heard the question clearly; (2) reading out the questions in a language that is easily understood by participants; (3) repeating the question, if necessary; (4) using local terms and giving sufficient pause, taking care not to rush through the questions.After all the PBS questions had been administered, the facilitator (1) collected the cards separately for each of the boxes: green, red, and white and (2) tallied and recorded the number of responses from each card in each of the colored boxes into a standard reporting form.All data generated through the PBS process were entered into a tablet by the study team using a standardized database created specifically for the ePBS. The data collection was facilitated using SurveyCTO (Dobility, Inc), a secure and scalable mobile data collection platform designed for researchers working in offline settings.

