### Target Sample Size Calculation

To be representative of each key population group, the study’s sampling strategy was based on probability sampling techniques that provided an equal chance to all members of the study populations, meeting defined inclusion criteria, to be included in the study. The determination of an appropriate sample size for a single study domain is usually based on the following considerations: (1) the number of measurement units in the population, (2) the parameter of interest, and (3) the degree of confidence by which the parameter is estimated and the desired level of precision.

One objective of our study was to estimate the HIV prevalence and incidence among female sex workers and men who have sex with men in Nairobi County. As such, sampling parameters were set with the prevalence and sample size having 95% statistical confidence, with a desired precision of +5% or –5%.

The sample size for PBS and BBS study was calculated using the following formula: *n* = [1.96^2^*p*(1 – *p*)(*DEFF*)]/*d*^2^. Where *p* is HIV prevalence, *DEFF* is the design effect of the sampling approach, and *d* is the desired precision.

The finite population correction factor is then applied to the derived sample size using the following formula: *nf* = (*n **
*N*)/[(*n* + (*n* – 1)]. Where *nf* is the sample size adjusted for finite population correction, *n* is the sample size required, and *N* is the population size.

To calculate the sample size for this ePBS study, we used the most recent estimate of HIV prevalence among female sex workers (26%) and men who have sex with men (12%) in Nairobi, as reported in a 2017 study conducted by NASCOP [7]. The sample size calculation was adjusted to accommodate an anticipated nonresponse rate of 15%. The final target sample size, adjusted for population size and nonresponse, for female sex workers was n=769 and for men who have sex with men was n=420. Ideally, each PBS session comprises 10 to 12 participants; the total target sample sizes for female sex workers and men who have sex with men were divided by 12 to determine the total number of PBS sessions required for each key population group, that is, 64 PBS sessions with female sex workers and 35 sessions with men who have sex with men.

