### Developing a Sampling Frame

#### Overview

The study used a 2-stage, random sampling approach. In the first stage, random locations (ie, places where female sex workers solicit clients or engage in sex and where men who have sex with men cruise or engage in sex) were selected from a previously validated list. In the second stage, participants were randomly selected from the locations on a randomly selected day of the week.

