#### Stage 2 Sampling

In stage 2 of sampling, each of the 99 randomly selected locations was randomly allocated to an assigned week and day on which potential participants were enrolled from the location. For example, data collection for this ePBS study was projected to take 30 days; for each location, 1 week (ie, from weeks 1 to 4 of the study period) was randomly selected first, followed by the random selection of 1 specific day within that chosen week. This process determined the precise week and day that each selected location was designated for the study. Ultimately, 10 to 12 potential participants were randomly approached by community researchers at the location on the specified day and week and invited to take part in the study.

This 2-stage sampling approach ensured that participants were representative of the total population of the key population group by geography (subcounty) and location typology across days of the week, yielding a comprehensive and diverse sample of participants from communities of female sex workers and men who have sex with men in Nairobi County.

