### Participant Enrollment and Data Collection Site Preparation

Potential participant enrollment occurred at selected locations on the allocated days of the week, according to the study’s sampling frame. Enrollment primarily occurred in the late afternoon or evening on the day of data collection to increase the likelihood of meeting a higher number of female sex workers or men who have sex with men in the location. Peer educators and outreach workers from the SWOP clinics facilitated the identification of potential participants within their own key population group. They were responsible for introducing potential participants to the study and assessing their eligibility. Any eligible individuals were provided with detailed information about ePBS. If eligible participants were interested in participating in the study, they were brought to the data collection site by peer educators and outreach workers. As much as possible, data collection occurred within the selected locations. Ahead of participant enrollment, the study team members scouted selected sites to identify suitable spaces for safe and confidential data collection. Team members were responsible for setting up stations for PBS and private, quiet locations for face-to-face structured interviews and biological sample collection. If the selected sites posed challenges (eg, logistical or safety challenges) for data collection, prescouted alternate locations nearby were used instead.

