## Discussion

### Overview

Joint United Nations Programme on HIV and AIDS encourages countries to annually measure outcomes using nimble, rapid, and low-cost methods [28]. Through this study, the novel ePBS method was implemented for the first time, which expands upon the traditional PBS method by integrating BBS and FGD modules with minimal requirements for additional resources. Furthermore, this innovative approach adopted robust sampling methods to ensure the representativeness required for a population-based survey, unlike the traditional PBS method, which uses program-based sampling approaches [7,23]. This approach included data gathered at the group level (PBS and FGD) and individual level (BBS), encompassing behavioral, biological, and structural aspects of a combination prevention approach, from a total sample of 1157 participants within a 30-day timeframe. This method significantly enhances the range of tools currently available to collect routine outcome data from HIV prevention programs. Importantly, the ePBS method empowered the research team to efficiently gather a rich data set comprising both quantitative and qualitative data for program optimization and expanded the understanding of local HIV epidemics among key populations. The inclusion of community researchers in the study team and the involvement of peer educators at the sampled locations fostered trust and instilled confidence among study participants, enhancing the study’s credibility, which is reflected in the study’s high response rate.

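### The selection of people within locations is described both as a random draw and as recruitment by the programme's own peer educators, so the equal-chance and representativeness claims are not secured for the coverage outcomes

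*Protocol article*

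**What the plan says.** Four places describe a probability design:

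- PBS Component, Sampling Procedure: "Potential participants are selected using a 2-stage, randomized, probability-based sampling procedure".
- Developing a Sampling Frame, Overview: "participants were randomly selected from the locations on a randomly selected day of the week".
- Stage 2 Sampling: "10 to 12 potential participants were randomly approached by community researchers at the location on the specified day and week".
- Target Sample Size Calculation, on the strategy as a whole: it "provided an equal chance to all members of the study populations, meeting defined inclusion criteria, to be included in the study".

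Other places describe recruitment by programme personnel:

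- PBS Component, Implementation Procedure: "Peer educators from SWOP mobilized 10 to 12 potential participants and invited them to participate in a PBS session".
- Participant Enrollment and Data Collection Site Preparation: "Peer educators and outreach workers from the SWOP clinics facilitated the identification of potential participants within their own key population group". The same people introduced the study, assessed eligibility and brought interested people to the site.
- Study Team, Composition: SWOP peer educators supported enrollment, and everyone on the teams apart from the qualitative researchers came from PHDA-SWOP clinic staff.

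The Results section plans weights for the sampling design and for unequal selection probabilities. The Discussion overview says the study "adopted robust sampling methods to ensure the representativeness required for a population-based survey", contrasts this with the programme-based sampling of the traditional method, and presents peer educators' involvement as a strength. The Limitations section does not mention selection by programme personnel.

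**The concern.** A random draw and mobilization by peer educators are different selection mechanisms, and the article attributes both to the same step. Which one operated matters most for coverage. The Study Setting section says the programme reaches its clients through peer educators and clinics. Outcomes for Measurement lists contact and utilization coverage among the outcomes, and the third research question asks for programme coverage. If the people who deliver contact also decide who enters the sample, those they already know may be over-represented, and coverage would look higher than it is.

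Design weights do not settle this. They correct for selection probabilities that are known, such as those arising from the location draw and the number taken per location. They cannot correct for a preference for known contacts that nobody recorded. The advantage claimed over programme-based sampling depends on how this step was done.

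The equal-chance sentence is a second inconsistency. If every eligible person had the same chance, no weights for unequal probabilities would be needed.

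**Working it through.** **The accounts side by side**

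| Question | Sampling sections | Implementation, enrollment and team sections |
|---|---|---|
| Who makes first contact? | Community researchers | SWOP peer educators and outreach workers |
| How is the person chosen? | At random | Identified, screened, mobilized and invited within the recruiter's own group |
| Link to the programme | Not stated | Peer educators and outreach workers of the SWOP clinics |

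Treating community researchers and peer educators as the same people does not remove the conflict. The Discussion overview names them separately. If the community researchers are instead the teams' outreach workers, the Composition section makes them clinic staff. On either reading programme personnel carried out the step, and the texts still disagree on whether chance or the recruiter decided who was invited.

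**Size of the risk**

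The article gives no figure for this bias, so there is none to reproduce. Inputs:

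- c, true contact coverage. 88% (female sex workers) and 76% (men who have sex with men) are the 2017 peer-educator contact levels in the Background. They are illustrative only, because the Discussion says the traditional method used programme-based sampling. 50% is an assumed lower value.
- k, how many times as likely a contacted person is to be invited as an uncontacted one. The article gives no value; this is an assumption.
- A yardstick of 5 percentage points, the precision set in Target Sample Size Calculation. It was set for HIV prevalence, not for coverage.

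Expected measured coverage is m = kc / (kc + 1 − c).

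| True c | k = 1 | k = 1.5 | k = 2 | k = 3 |
|---|---|---|---|---|
| 50% | 50.0% | 60.0% | 66.7% | 75.0% |
| 76% | 76.0% | 82.6% | 86.4% | 90.5% |
| 88% | 88.0% | 91.7% | 93.6% | 95.7% |

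The k that raises coverage from c to t = c + 0.05 is k = t(1 − c) / [c(1 − t)]:

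- c = 50%: 0.55 × 0.50 / (0.50 × 0.45) = 1.22
- c = 76%: 0.81 × 0.24 / (0.76 × 0.19) = 1.35
- c = 88%: 0.93 × 0.12 / (0.88 × 0.07) = 1.81

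Solving the first formula for c gives the correction c = m / [m + k(1 − m)]. For example, m = 88% with k = 2 returns 0.88 / (0.88 + 0.24) = 78.6%.

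**Do the reported response rates exclude this?**

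No. 759/769 and 398/420 use as denominators the target sample sizes, which already contain the 15% nonresponse allowance. They show enrollment against target, not acceptance among people approached, and say nothing about who was approached.

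**The case against.** The enrollment section says peers facilitated identification and introduced people to the study; nowhere does it say they chose people they knew. The passages could describe peers giving access to people approached at random, as Stage 2 states. Then k = 1 and there is no bias. An article may also leave the within-location count or interval rule to the full protocol. In criminalized groups, peer involvement has real safety and trust reasons behind it.

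Most of this stands as a limit on what can be concluded. It does not remove the inconsistency, because neither the Implementation Procedure nor the enrollment section says that peers only introduced people already drawn.

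Several stronger readings are tempting but unsupported:

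- That coverage **is** biased upward. This is the expected direction, not a documented one.
- That testing, PrEP, treatment and condom outcomes are inflated in the same way. Nothing in the article establishes this.
- That locations were drawn without regard to size, so that chances differ by a large known multiple. Stage 1 Sampling mentions verified size estimates and neither states nor excludes size-proportional selection. No location-specific sizes are given, and the planned weights could address this part.
- That coverage should be reported as an upper bound whatever the reconciliation shows. This presumes the direction and ignores other errors, such as the self-report acknowledged in Limitations.
- That the recruiters should have been different people. Data collection is complete, and the inconsistency can be resolved without changing the recruitment.

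**Conclusion.** The inconsistency is real and lies in the current text: one selection step has two incompatible descriptions, and the equal-chance sentence conflicts with the planned weights. The consequence for coverage is a risk, not a finding of bias. If peers chose participants, a preference of about 1.22-fold to 1.81-fold for known contacts, over true coverage of 50% to 88%, would be enough to move contact coverage by 5 points. At 88% coverage a 1.5-fold preference moves it by only 3.7 points (91.7 − 88.0). All of this rests on an assumed k and illustrative coverage levels; with k = 1 the effect is zero. Until the passages are reconciled, the article does not secure its claim to a representative probability sample for contact and utilization coverage.

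**What to change.** 1. Reconcile Implementation Procedure, Stage 2 Sampling and Participant Enrollment so that they state, in the same terms, who selected people at a location and by what rule.
2. In Target Sample Size Calculation, replace the equal-chance wording with a statement that selection probabilities were unequal and are corrected by weights.
3. If programme peers chose participants:
   - describe stage 2 as peer-facilitated;
   - qualify the probability-sample and representativeness claims in Sampling Procedure, Stage 2 Sampling and the Discussion overview;
   - add recruitment by programme personnel to Limitations, with reference to the coverage outcomes;
   - report contact and utilization coverage with a sensitivity table of m / [m + k(1 − m)] for k from 1 to 3, with k labelled as an assumption.
4. If peers only introduced people already drawn at random, say so; step 3 is then unnecessary.

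The cost is wording and, in the case of step 3, one table. No new data are needed, and analysis was still under way when the article was written. The downside is a weaker representativeness claim.
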